**PROTOCOL VERSION HISTORY AND AMENDMENTS**

| Date | Version Number | Description of Modifications                                                                    |
|--------------------|------------------------------|---------------------------------------------------------------------------------------------------------------|
| January 13, 2013   | 1.0                          | Included original quasi-experimental study design.                                                            |
| May 30, 2013       | 2.0                          | Changed design to randomized controlled trial.                                                                |
| July 30, 2013      | 2.1                          | Changed consent mechanism from opt-in to opt-out.
Incorporate use of refined Denver HIV Risk Score (DHRS). |
| November 26, 2013  | 2.2                          | Amended exclusion criteria to include occupational HIV exposure.                                              |
| March 20, 2014     | 2.3                          | Updated HIV testing methodologies and several methodological clarifications.                                  |
| April 1, 2014      | 2.4                          | Amended exclusion criteria to remove prisoners.                                                               |
| January 29, 2015   | 2.5                          | Amended consent procedures to allow for waiver of consent for longitudinal follow-up.                         |

**ABBREVIATIONS AND DEFINITIONS**

AIDS – Acquired Immunodeficiency Syndrome  
 BRST – Behavioral Risk Screening Tool  
 CDC – Centers for Disease Control and Prevention  
 CDPHE – Colorado Department of Public Health and Environment  
 CER – Cost-Effectiveness Ratio  
 CHIP – Children’s Hospital Colorado Immunodeficiency Program  
 CI – Confidence Interval  
 COMIRB – Colorado Multiple Institutional Review Board  
 DHMC – Denver Health Medical Center  
 DHRS – Denver HIV Risk Score  
 ED – Emergency Department  
 EDWIN – Emergency Department Work Index  
 HAART – Highly Active Antiretroviral Therapy  
 HIV – Human Immunodeficiency Virus  
 ICER – Incremental Cost-Effectiveness Ratio  
 ILHE – Individual Level Health Education  
 IQR – Interquartile Range  
 IRB – Institutional Review Board  
 MSM – Men Who Have Sex with Men  
 PCM – Prevention Case Management  
 RR – Risk Ratio  
 SD – Standard Deviation  
 SFTP – Secure File Transfer Protocol  
 UCH – University of Colorado Hospital  
 USPSTF – United States Preventive Services Task Force  
 WHO – World Health Organization

**APPENDIX**

## **1. SPECIFIC AIMS AND HYPOTHESES**

Early identification of undiagnosed HIV infection remains a critical public health priority. The research proposed in this project will evaluate the effectiveness of 3 rapid HIV screening methods, including a novel targeted strategy, in urban emergency department settings in the United States. The results of this study will help inform public health practices of how best to identify patients with whom to test for HIV infection in this important clinical setting, in an effort to improve the timeliness of diagnosis and linkage-to-care.

### **Specific Aim 1: To evaluate and compare the effectiveness of targeted and nontargeted rapid HIV screening strategies when fully-integrated into ED settings**

**Hypothesis 1a:** Enhanced targeted rapid HIV screening (using the refined DHRS as a novel tool to identify high-risk patients) is significantly associated with new HIV diagnoses when compared to nontargeted rapid HIV screening.

**Hypothesis 1b:** Traditional targeted rapid HIV screening (using previously-recommended risk characteristics to identify high-risk patients) is significantly associated with new HIV diagnoses when compared to nontargeted rapid HIV screening.

### **Specific Aim 2: To measure and compare programmatic costs associated with implementation of targeted and nontargeted rapid HIV screening strategies when fully-integrated into ED settings**

**Hypothesis 2:** Enhanced and traditional targeted rapid HIV screening is more cost effective per newly-identified HIV-infected patient than nontargeted rapid HIV screening from the institutional perspective.

### **Specific Aim 3: To measure and compare ED operational processes and crowding when targeted and nontargeted rapid HIV screening strategies are fully-integrated into ED care**

**Hypothesis 3:** Enhanced targeted rapid HIV screening is not associated with: **(a)** longer patient waiting times; **(b)** longer patient length of stay times; **(c)** longer patient ED boarding times; **(d)** larger proportion of patients who leave prior to completing medical evaluation; or **(e)** greater overall crowding when compared to traditional targeted rapid HIV screening or nontargeted rapid HIV screening.

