## 4. METHODS

### A. Study Design

#### Specific Aim 1

For this aim, we will perform a multi-center, prospective, randomized, controlled clinical trial to evaluate the effectiveness of three distinct HIV screening approaches. Implementation of a randomized controlled trial will incorporate use of “pragmatic” or effectiveness methodologies, and will allow us to compare

[figure not shown]

the effectiveness of the three screening approaches while minimizing threats to internal validity. Patients will be screened using one of three interventions in a 1:1:1 random sequence; patients will therefore be offered HIV testing based on the results of which screening arm they are assigned, and in the case of the two screening tools, the results of risk assessment. All screening methodologies will be integrated into electronic patient triage systems at each site; as such, the actual randomization process will also be integrated into the electronic system, allowing for real-time concealed random allocation (**Figure 1**). Nurses who perform screening and all ED staff (e.g., physicians, nurses, and technicians) will understand the conceptual goals of the project but will be blinded to the specific hypotheses, and patients will be completely blinded to the purpose of the study.

All of the participating sites have established ED-based HIV testing programs, and all of the testing procedures that occur after patients are identified for HIV testing (i.e., consent for the test, performance of the test, results disclosure, linkage to care, etc.) will have been integrated into clinical processes within each ED as standards of care. The specific interventions being evaluated in this

study relate only to how patients are identified for and offered HIV testing. The standard process used by the DHMC ED and the integration of the three study interventions is described by the “ED Rapid HIV Screening Workflow” figure (**Appendix**).

#### Specific Aims 2 and 3

For these aims, we will perform prospective cohort studies nested in the clinical trial described above.

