## **D. Interventions**

We will perform a prospective clinical trial at four institutions across the United States. Each study site will enroll consecutive eligible patients and randomize them to one of three rapid HIV screening interventions (described below), all of which are utilized as either local or national standards of care. The three screening interventions will be fully integrated into electronic patient screening and tracking systems in each ED and integrated into triage processes. Eligible patients will be screened by triage nurses in accordance with institutional standards of care; as part of this process, patients will be screened for HIV infection using one of the three screening tools in a 1:1:1 random sequence as determined by a random sequence generator built into the electronic patient screening systems. Patients will then be offered voluntary rapid HIV testing based on the screening arm they are assigned (i.e., patients randomized to the nontargeted HIV screening arm will be offered HIV testing without assessment of risk, whereas those randomized to the two targeted screening arms will be offered HIV testing only if they are identified as being at increased risk for HIV infection). To maximize generalizability to ED settings, screening will be performed 24 hours per day for the entire study enrollment period and all screening and testing methods will be fully integrated into ED operations.

### Specific Aim 1

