where 0 – 20 is considered “not busy”, 21 – 60 considered “busy”, 61 – 100 considered “very busy”, 101 – 140 considered “crowded”, 141 – 180 considered “dangerous”, and 181 or greater considered “disaster”. EDWIN and NEDOCS have been compared head-to-head and have both been shown to be valid and comparable metrics for quantifying ED crowding.

Values for each of the four basic time metrics will be collected real-time for all patients enrolled into the study using electronic patient tracking systems. Patients who register for evaluation in each ED on a daily basis include time stamps related to initiation of medical screening, ED bed assignment, patient discharge or admission to the hospital and, if admitted to the hospital, inpatient bed assignment. Because EDWIN and NEDOCS rely on point-in-time sampling and at the level of the ED, it is not feasible to measure their variables on a continuous, real-time basis. However, we will calculate the fifth ED metric, either EDWIN or NEDOCS, at the time each patient begins medical screening and when he or she is discharged. The difference between these data will be used as a covariate in the analyses for this aim as described below.

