Process metric variables for all enrolled patients will be compared between study arms. Because the time and EDWIN or NEDOCs metrics are continuous, they will be reported as means with SDs or medians with IQRs. Bivariate analyses will be used to estimate statistical differences between each process metric and the three HIV screening interventions. Because we propose measuring five ED process metrics, we have defined statistical significance for this part of the analyses to be a Bonferroni-adjusted p-value <0.01. Also, hierarchical multivariable linear regression analyses will also be used to estimate associations between each of the interventions and continuous process metrics, while accounting for clustering at the institution level and adjusting for overall ED crowding as measured by the difference in either EDWIN or NEDOCs for the duration of the patient's visit. If necessary, continuous data will be transformed and multiple imputation will be used in instances where data are missing. The primary unit of analysis will be patient visits.

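### Hypothesis 3(e) is not testable as planned: comparing EDWIN/NEDOCS between concurrent, individually randomised arms does not identify any strategy's effect on overall ED crowding

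*Protocol*

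**What the plan says.** Specific Aim 3 sets out to measure and compare operational processes and crowding under the three strategies. Part (e) of Hypothesis 3 is that enhanced targeted screening is not associated with "greater overall crowding when compared to traditional targeted rapid HIV screening or nontargeted rapid HIV screening".

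On allocation, Section 4.D says "Each study site will enroll consecutive eligible patients and randomize them to one of three rapid HIV screening interventions" and that "screening will be performed 24 hours per day for the entire study enrollment period". Section 4.A gives the ratio as 1:1:1. No ED and no period is reserved for one strategy.

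On the metric, Section 4.F (Aim 3) builds EDWIN from patients present, physicians on duty, beds and admitted patients awaiting a bed. NEDOCS uses total ED patients and beds, boarders, ventilated patients and the longest waits. Neither formula contains study arm, and the section itself notes that "EDWIN and NEDOCS rely on point-in-time sampling and at the level of the ED". The score is taken twice per patient, at the start of medical screening and at discharge, and the difference is to serve as a covariate.

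On the analysis, Section 4.H (Aim 3) says "Process metric variables for all enrolled patients will be compared between study arms". It names EDWIN or NEDOCS among those metrics, tests each metric against the three interventions, and sets p<0.01 because there are five. It also adjusts the continuous metrics for the change in the crowding score. The Aim 3 limitations in Section 5.H cover data acquisition, coding and missing data only.

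**The concern.** The hypothesis asks what happens to a department that adopts a strategy. The comparison is between patients who share one department at the same time. If one strategy slows the ED, the higher score is recorded for patients of all three arms who are assessed at that moment, so the extra load does not separate the arms.

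This matters because 3(e) predicts no association. A non-significant comparison would naturally be reported as support for the claim that enhanced targeted screening does not add to crowding, and a significant one as evidence on that claim. The design supports neither statement.

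A linked problem is the covariate. The start-to-discharge difference in the score is measured after randomisation and depends on how long the patient stays, which is itself one of the outcomes to be adjusted.

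**Working it through.** **The plan's own figure.** Five metrics under Bonferroni give 0.05/5 = 0.01, which reproduces the stated level. With crowding removed, 0.05/4 = 0.0125.

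**What each snapshot can show.**

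1. *Start of screening.* The score is fixed before the patient's assigned screening can affect the ED. Provided allocation does not depend on the state of the ED, its expected between-arm difference is zero, however much crowding any strategy causes.
2. *Discharge, and the change.* At any moment there is one score for the whole ED. Two patients get different discharge scores because they leave at different times. An arm that alters length of stay shifts the sampling time, so a small contrast can arise. That contrast reflects when patients leave, not crowding caused by their arm.

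**Illustration.** All inputs here are assumptions except the NEDOCS occupancy coefficient of 85.8 (Section 4.F): one ED, 50 beds, 200 visits a day with a daily cycle, median stay 210 minutes before any added time, and only the occupancy term of NEDOCS. One arm adds 10, 30 or 60 minutes of stay. There were 60 runs of 150 days with concurrent 1:1:1 allocation.

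The whole-ED effect if every patient followed the slower strategy can be checked by hand as arrivals per minute × added minutes × 85.8/50:

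- 10 min: (200/1440) × 10 × 1.716 = 2.38
- 30 min: (200/1440) × 30 × 1.716 = 7.15
- 60 min: (200/1440) × 60 × 1.716 = 14.30

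| Added stay | Whole-ED effect, simulated | Between-arm, start (SE) | Between-arm, change (SE) |
|---|---|---|---|
| 10 min | 2.58 | -0.015 (0.044) | -0.087 (0.045) |
| 30 min | 6.84 | 0.026 (0.033) | -0.250 (0.044) |
| 60 min | 14.01 | 0.038 (0.039) | -0.667 (0.042) |

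Units are NEDOCS points, slower arm minus another arm. SEs are Monte Carlo. The start contrast is zero within error. The change contrast is a small fraction of the whole-ED effect and has the opposite sign.

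**Could the change contrast be significant?** The SD of one run is SE × √60: 0.349, 0.341 and 0.325. A run has about 200 × 150 = 30,000 visits. Section 5.C allows up to 120,000 subjects, four times as many, so the SD halves to about 0.174, 0.170 and 0.163. Then z is about 0.5, 1.5 and 4.1, against 2.58 for two-sided p<0.01. Under these inputs the test would usually be null for the two smaller effects. For the largest it would usually be significant, with the slower arm looking less crowded.

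**The case against.** *Crowding is only a covariate.* Section 4.F does give the difference that role. But Hypothesis 3(e) makes crowding a claim, and Section 4.H counts it among the five metrics tested between arms. It is both.

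*A later analysis plan can handle this.* The protocol already fixes the hypothesis, the unit of allocation, the metric and the comparison. No refinement of that comparison recovers a department-level effect.

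*The arms do not share a single value, because each visit has its own two snapshots.* This stands. A reader might infer that a no-difference result is guaranteed, or that the analysis will confirm 3(e) however much crowding a strategy causes. The protocol does not support that. It is exact only for the start score. The change can differ by arm and, as the last step of the check shows, could cross p<0.01 in the wrong direction.

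*The true effect may be small.* This also stands. Section 4.I assumes 25% versus 5% test completion, and Section 5.D gives a 30 to 45 minute turn-around at one site. If every test prolonged the stay by its full turn-around, the mean difference would be 0.20 × 30 = 6 to 0.20 × 45 = 9 minutes, leaving out questionnaire time, which is not stated. On the assumed ED this is (200/1440) × 6 × 1.716 = 1.4 to (200/1440) × 9 × 1.716 = 2.1 NEDOCS points, against category bands about 40 points wide. That limits the practical loss but does not make the comparison informative.

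*Waiting, stay and boarding times.* A reader might infer that these fail in the same way. They do not. They are recorded per patient and remain measurable by arm. Shared queues may dilute the differences, but by an amount that the protocol gives no means to quantify.

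**Conclusion.** The point holds as a matter of identification. With concurrent individual allocation and a whole-ED score, the comparison in Section 4.H does not estimate any strategy's effect on overall crowding, so neither a null nor a significant result is evidence for or against 3(e). This rests on the protocol's text and on allocation being independent of the state of the ED. The simulated sizes are illustrative and rest on assumed inputs.

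The reach is limited to one of five sub-hypotheses in the third aim, together with the choice of crowding covariate for the other metrics. Hypotheses 3(a) to (d) stay testable as effects of a patient's own assignment, and the primary outcome is untouched. The move from 0.01 to 0.0125 is bookkeeping and carries no weight in the argument.

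**What to change.** - Remove part (e) from Hypothesis 3 and the between-arm crowding test from Section 4.H.
- Make the Aim 3 title, Section 4.E (Aim 3) and the five-metric description in Section 4.F (Aim 3) consistent with four compared metrics. Set the significance level to 0.05/4 = 0.0125 if the Bonferroni rule is kept.
- Report EDWIN or NEDOCS descriptively by site.
- In Sections 4.F and 4.H, adjust the remaining metrics only for the crowding score at screening start. Give the reason: the start-to-discharge difference arises after randomisation and depends on length of stay.
- In the Aim 3 limitations (Section 5.H), state that between-arm differences in waiting, stay and boarding estimate the effect of a patient's own assigned screening, not of a department adopting that strategy.

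The cost is wording and the loss of one secondary sub-hypothesis. Testing a department-level effect would need whole EDs or time blocks allocated to a single strategy, which is a different design.

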## **2. BACKGROUND, SIGNIFICANCE, AND RATIONALE**

In the United States, over 1.1 million individuals are infected with HIV, approximately 250,000 remain undiagnosed, and 50,000 new infections occur annually. These estimates have not changed dramatically over the last 15 years and new diagnoses appear to be on the rise in certain populations. Although the largest group of persons newly-infected remains men who have sex with men (MSM), new cases continue to be found disproportionately in racial/ethnic minorities, adolescents, and young adults. Undiagnosed HIV infection continues to be disproportionately represented in the ongoing epidemic and its early identification remains a critical public health priority.

Testing for HIV infection is the first in a series of important interventions aimed at impacting the epidemic. Identifying individuals with HIV infection provides a critical opportunity to link them into care where treatment with antiretroviral medications reduces viral loads, thus slowing disease progression and reducing infectivity. Also, knowing one's serostatus attenuates individual behaviors that contribute to transmission of the virus. Between 2006 and 2011, the Centers for Disease Control and Prevention (CDC) and the White House released numerous recommendations and strategies in an effort to increase testing rates and, therefore, identification of undiagnosed HIV infection. The CDC strongly recommends

nontargeted opt-out HIV screening in all healthcare settings where the undiagnosed prevalence is  $\geq 0.1\%$ , and the National HIV/AIDS Strategy recommends prevention methods that combine "... scientifically proven, cost-effective, and scalable interventions targeted to the right populations in the right geographic areas..." High impact prevention prioritizes effectiveness and costs, feasibility of implementation, and coverage of target populations. In this context, HIV testing remains the principal means of secondary prevention of HIV infection.

Emergency departments (EDs) are a major focus of HIV testing efforts in the United States, prompted by the fact that over 120 million ED visits occur annually, they serve substantial numbers of underserved patients, and are the most common site of missed opportunities for diagnosing HIV infection. Given these features, EDs are an ideal setting to identify patients with undiagnosed HIV infection. Recognizing its potential value, in 2001 the CDC endorsed ED-based HIV screening as part of the national strategy to contain HIV infection; unfortunately, several challenges remain. From 1993 through 2005, only approximately 0.4% of all ED patients had HIV testing performed. With more aggressive initiatives, including the 2006 CDC recommendations, and several feasibility studies, a larger number of EDs in the United States have incorporated HIV testing into routine practice. However, most EDs still rely primarily on diagnostic testing (74% in academic EDs and 62% in non-academic EDs) with relatively sparse uptake of nontargeted screening (16% in academic EDs and 6% in non-academic EDs).

In 2007, Rothman *et al.* published a conceptual framework of ED-based HIV testing strategies. Within this framework, the following 3 HIV testing approaches were described: (1) diagnostic testing (defined as testing performed by a clinician based on clinical signs or symptoms); (2) targeted screening (defined as testing high-risk subpopulations based on identification of patient characteristics associated with HIV infection); and most recently; (3) nontargeted screening (defined as testing all individuals regardless of risk).

Diagnostic testing is an important method of identifying patients with HIV infection in the ED. This approach, introduced by the CDC in 1986, is inherently understood by clinicians because of its potential to directly impact patient care. However, even when such testing is available, many clinicians do not maintain a sufficiently high suspicion for HIV infection among their patients, thus dramatically limiting the effectiveness of this approach. Targeted screening allows for risk-based testing of patients, a prevention approach most would consider intuitive when attempting to impact an epidemic. This approach, however, relies on the assumptions that characteristics of the epidemic are fully appreciated in the targeted population, identifying patients who are at risk is possible, and sufficient resources are available to perform broader testing. Nontargeted screening, on the other hand, was recommended in an effort to provide all patients, regardless of risk, the opportunity to be tested for HIV infection. Implementation of such large preventive interventions in busy EDs has proven difficult, with success limited to relatively few interested institutions with dedicated resources. Since 2006, 11 studies have evaluated nontargeted HIV screening in an ED setting. Although all have demonstrated the ability to identify patients with HIV infection, the effectiveness of such screening can best be judged as modest.

In 2007 the World Health Organization (WHO) released its guidance on provider-initiated HIV testing in healthcare facilities, and in contrast to the 2006 CDC recommendations, recommended more selective HIV testing (i.e., diagnostic testing or targeted screening) in settings where the HIV epidemic was concentrated. According to WHO definitions, even the highest prevalence areas in the United States are considered concentrated. Similarly, in 2007, the United States Preventive Services Task Force (USPSTF) recommended targeted HIV screening as the principal approach to HIV testing, based in part, on the assessment that little empiric evidence existed to support a broader HIV screening initiative. More recently, the USPSTF revised their recommendations to state, "clinicians [should] screen for HIV infection in adolescents and adults aged 15 to 65;" however, in their document, the Task Force does not explicitly

define how screening should be performed. Although there is now apparent synergy between the CDC, USPSTF, and the National HIV/AIDS Strategy, relatively little has been done to understand which screening approach in EDs is most effective and efficient, especially when resources are constrained. Critical barriers to progress in this field remain and result from the paucity of empiric evidence to drive practice change. While research has demonstrated ED capacity to identify unrecognized HIV infection, limited research has compared clinical outcomes, programmatic methods, or cost effectiveness of different HIV screening approaches and their impact on ED services. Public health recommendations, including those on HIV screening, must be rooted in the results of rigorous, large-scale, comparative effectiveness research. Recognizing the practical limitations of “routine screening” in clinical settings is important, while striving to balance efficient resource utilization with effective patient selection and testing methods. Expanded testing programs is important, although further research is necessary to prioritize effectiveness and costs, feasibility of implementation, and coverage of target populations. What remains unknown is whether nontargeted HIV screening is the optimal method of identifying patients with HIV infection or whether other approaches (e.g., targeted strategies) may be more effective. This project will address these knowledge gaps with high-quality effectiveness research, and will provide the basis for how HIV screening should be performed in ED settings.

